Participants will be questioned at enrollment about their functional status along with other baseline medical conditions such as co-morbidities using a standardized questionnaire. Functional status is the individual's ability to perform normal activities of daily living. We will use the index from the Vulnerable Elders Survey (7) along with individual elements from other indices and test their association with ARI to determine if experiencing ARIs or SARIs impacts functional status. Cognitive function will be self-assessed as other measures require trained medical personnel to implement. Vulnerable Elders Survey (VES-13) is a function-based questionnaire that was developed to screen elderly 65 years of age or greater in the community to determine their risk for health deterioration (7, 8). The questionnaire asks elderly to self-report their age, health, limitations in physical function and functional disabilities, and takes an average of less than five minutes to complete(7, 8). This tool can be administered over the phone or in person. Each response to each question on the form has a point value attached ranging from 0 to 3 points, and it is scored by adding up points based on the responses received, up to 10.(8) Scores  $\geq 3$  indicate frailty associated with increased mortality. The test has been shown to be reliable (7, 9, 10). The same functional status measurements were used in a companion study which assessed whether functional status correlated with obtaining flu vaccine and has already been translated into Thai. Using the same functional status measurement tool in this study will allow us to compare outcomes between both studies and build upon prior conclusions. Participants will be asked to re-take the functional status VES-13 questionnaire every six months during the study period to measure changes in functional status over time.

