In order to measure the impact of the first episode of ARI or SARI on functional status, we will conduct a nested case-control study of participants recovering from an ARI or SARI. Participants who experience their first ARI or SARI after enrollment will be matched with cohort participants who have not yet experienced an ARI or SARI based on age ( $\pm 5$  years), sex, influenza vaccination and most recent functional status measurement. Interviews will be conducted three to four weeks after the onset of ARI or SARI in the case and both cases and controls will be compared with respect to changes in functional status measurement (VES-13 score  $\geq 3$ ).

Elderly with COPD: In the standardized baseline questionnaire assessing functional status and medical conditions, participants will be asked whether they have been diagnosed with COPD. If they do, at the end of two years, the number of outpatient visits and inpatient admissions for exacerbations of COPD will be determined (by directly observing their medical records). A COPD exacerbation is defined as “a sustained worsening of the patient's condition, from the stable state and beyond normal day-to-day variations that is acute in onset and may warrant additional treatment in a patient with underlying COPD” (11). We will use the collected nasal self-swabs or healthcare worker collected nasopharyngeal swab taken when the participant was experiencing an ARI or SARI to confirm whether the COPD exacerbations the participant experienced were influenza-associated. At the end of the study, the incidence of all-cause COPD exacerbations and laboratory confirmed influenza-associated COPD exacerbations among the elderly with COPD who fit the ARI or SARI case definitions will be calculated. The incidence among those who were vaccinated will be compared to those who were not vaccinated.

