#### **7.1.5 Number of participants**

Sample size for cohort: The cohort sample size is calculated assuming a 50% vaccination rate, 80% power, a probability of committing a type I error of 5% and an incidence of influenza-associated ARI of 6% per year. With an expected VE of 40% based on our population's age and past studies (12, 16, 17), the required sample size is 2,724. Given a 15% loss to follow-up, a total of 3,133 persons should be enrolled, and assuming a 10% refusal rate, a total of 3,446, or, for simplicity, 3,500 individuals need to be selected

These sample sizes were calculated in OpenEpi.com(47) using the Fleiss Method with a correction factor as follows:

Fleiss Method:

$$n_1 = \frac{[Z_{\alpha}\sqrt{(r+1)\bar{p}\bar{q}} + Z_{1-\beta}\sqrt{rp_1q_1 + p_2q_2}]^2}{r(p_1 - q_1)^2}$$

$$n_2 = rn_1$$

where  $n_1$  is the number of cases and  $n_2$  is the number of controls,  $\bar{p}$  is the average exposure in the population,  $\bar{q}$  is  $1-\bar{p}$ ,  $p_1$  is the proportion of cases with the exposure,  $q_1$  is  $1-p_1$ ,  $p_2$  is the proportion of controls with exposure and  $q_2$  is  $1-p_2$ .

To account for the use of a normal distribution to approximate a binary function, a continuity correction is applied to  $n_1$  as follows to calculate the final sample size,  $n_{cc}$ :

$$n_{1cc} = \frac{n_1}{4} \left[ 1 + \sqrt{1 + \frac{2(r+1)}{n_1 r |p_2 - p_1|}} \right]^2$$

$$n_{2cc} = rn_{1cc}$$

where  $n_{1cc}$  and  $n_{2cc}$  are the corrected sample sizes of  $n_1$  and  $n_2$ , respectively.

Sample size for changes in functional status related to ARI or SARI: We will select matched pairs and compare functional status (measured on a 10 point scale by the VES-13) three-four weeks after the onset of an influenza-associated ARI or SARI to a control who has not had an ARI or SARI. As functional status is measured on continuous scale of 1-10, a matched dependent  $t$  test is used to compute sample sizes. We have used the PROC POWER procedure in SAS

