([http://support.sas.com/documentation/cdl/en/statug/67523/HTML/default/viewer.htm#statug\\_power\\_overview.htm](http://support.sas.com/documentation/cdl/en/statug/67523/HTML/default/viewer.htm#statug_power_overview.htm)) to calculate the required sample sizes. Assuming a mean score of 4 for the controls and 5 for the cases (higher VES-13 index indicates lower functional status), and standard deviation of 3 for the difference between the two means, a type I error rate of 0.05, correlation of 0.2 and power of 80%, we require 115 in matched pairs (230 in all).

Sample size for seroconversion: Seroconversion for secondary objective 2.2 will be assessed in a sub-sample of participants. We expect seroconversion rates of 30-50% among those vaccinated. In order to calculate a proportion of 50% plus or minus 5%-pts, we need 384 individuals who intend on becoming vaccinated. We will enroll them sequentially.

$$\frac{[Np(1 - p)]}{d^2 / 1.96^2 (N - 1) + p(1 - p)}$$

Where  $N$  is the population size,  $p$  is the estimated proportion,  $d$  is the absolute precision. In this study,  $N$  is the size of the elderly population in the two districts, approximately 15,000;  $p$  is 0.5 and  $d$  is 0.05.

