### **For secondary objective 2.1 (Functional status)**

Participants will be scored on their VES-13 results every six months. The Vulnerable Elders Survey (VES-13) is a function-based questionnaire that was developed to screen elderly 65 years of age or greater in the community to determine their risk for health deterioration (7, 8). The questionnaire asks elderly to self-report their age, health, limitations in physical function and functional disabilities, and takes an average of less than five minutes to complete(7, 8). This tool can be administered over the phone or in person. Each response to each question on the form has a point value attached ranging from 0 to 3 points, and it is scored by adding up points based on the responses received, up to 10.(8) Scores  $\geq 3$  indicate frailty associated with increased mortality.

In order to measure the impact of the first episode of ARI or SARI on functional status, we will conduct a nested case-control study of participants recovering from an ARI or SARI. Participants who experience their first ARI or SARI after enrollment will be matched with one cohort participant who has not yet experienced an ARI or SARI based on age ( $\pm 5$  years), sex, influenza vaccination and most recent functional status measurement. Interviews will be conducted three to four weeks after the onset of ARI or SARI in the case and both cases and controls will be compared with respect to changes in functional status measurement using a multinomial logistic regression to control for other potential confounders. Beginning from January 2016, when a complete dataset for vaccination and functional status will be available, these interviews will be conducted until the required sample size of 115 matched pairs of cases and controls are met.

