## **7.9 Data Analysis**

In order to evaluate the primary research question – the vaccine effectiveness of the inactivated trivalent IIV3 vaccine in the elderly - we will use Poisson regression with person-time at risk as an offset. The outcome variable will be the number of influenza associated ARI or SARI events in each given year of life among 2 groups, elderly who have been vaccinated with IIV3 and elderly who have not. The resulting count data will account for multiple outcomes in the same participant. We will also employ GEE methodology to the Poisson regression to account for geographical clustering by cases and correlation between outcomes in individuals with repeated measures. We can control for other predictive variables that may be associated with

underlying disease such as age, co-morbidities and distance to health facility. To reduce any potential non-random loss-to-follow up bias, we will use propensity score matching in addition to controlling for confounders. To address the other primary study question regarding cost, we will obtain estimates of direct and indirect costs from each of the groups and apply differences to the adjusted risks to arrive at the adjusted cost differences between elderly who have been vaccinated and elderly who have not been vaccinated.

In order to measure the effect ARI and SARI have on functional status (secondary objective 2.1) we will compare change in functional status among those that did and did not experience ARIs or SARIs by matching participants to one control when they become sick to see if there is a significant difference in functional status measurements. We will use a nested case control study to compare the two groups. By matching those who experienced a first ARI or SARI with those who had not on age ( $\pm 5$  years), sex, influenza vaccination and most recent functional status measurement ( $\pm 1$  point), we can account for unknown confounders that may cause a change in functional status while controlling for known confounders.

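### The functional-status outcome for objective 2.1 is defined inconsistently: section 3.1.4 ties it to the VES-13 ≥3 frailty cut, but the 115 pairs were sized on the full score, and on the cut they give roughly 50–60% power, not 80%

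*Protocol*

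**What the plan says.** The protocol describes the outcome of the functional-status sub-study (secondary objective 2.1) in several places.

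- **Section 3.1.4 (Functional Status):** "both cases and controls will be compared with respect to changes in functional status measurement (VES-13 score" ≥3). The same section says that scores of 3 or more "indicate frailty associated with increased mortality", so 3 is a boundary for a state, not for an amount of change.
- **Section 7.1.5 (sample size):** "As functional status is measured on continuous scale of 1-10, a matched dependent" t test is used. The inputs are "Assuming a mean score of 4 for the controls and 5 for the cases", a "standard deviation of 3 for the difference between the two means", and "a type I error rate of 0.05, correlation of 0.2 and power of 80%, we require 115 in matched pairs (230 in all").
- **Section 7.5.1 (For secondary objective 2.1):** "both cases and controls will be compared with respect to changes in functional status measurement using a multinomial logistic regression". No cut is attached to this sentence and no outcome categories are given. Interviews continue until 115 pairs are reached.
- **Section 7.5.2 (Functional status sub-study):** cases are interviewed to obtain their VES-13 score, again with no cut.
- **Section 7.9 (Data Analysis):** cases and controls are compared on functional status measurements without a cut. Matching on the "most recent functional status measurement" is given a tolerance of ±1 point.

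**The concern.** Read together, these sections allow a binary outcome (frail or not), a categorical one (multinomial) and a numerical one (paired t test). Only the last has a sample size behind it.

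The binary reading also fits poorly with the protocol's own planning values. A cut at 3 lies below the mean of 4 assumed for people who have had no illness. Someone who goes from 4 to 8 is at or above 3 both times and shows no change of status. With a ±1 tolerance, a person at 2 can be matched to a person at 3, so the pair already differs on ≥3 status before any illness effect.

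What is at stake is the sub-study's ability to detect the one-point effect it was planned around. Because interviewing stops at 115 pairs, a loss of power from the choice of outcome would not be made up later.

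**Working it through.** **Inputs (section 7.1.5).** Control mean 4, case mean 5, SD 3, correlation 0.2, type I error 0.05, power 80%, 115 pairs. The cut of 3 comes from section 3.1.4. Sidedness is not stated; two-sided is assumed and reproduces the figure.

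**Step 1: reproduce the 115 pairs.** With 3 as the SD of each person's score, the SD of the within-pair difference is √(2 × 9 × (1 − 0.2)) = √14.4 = 3.795. A two-sided paired t test for a difference of 1 then needs 115 pairs (power 0.800; the normal approximation gives 114). If 3 is read literally as the SD of the difference, the answer is 73 pairs. The stated figure therefore belongs to a full-score comparison with a per-person SD of 3.

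**Step 2: share of controls already at or above 3.** The protocol gives no distribution, so a range of shapes was tried at mean 4, SD 3:

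| Assumed shape | Share ≥3 |
|---|---|
| Normal, cut at 3: Φ((4 − 3)/3) | 63% |
| Normal, cut at 2.5 for whole-number scores: Φ(1.5/3) | 69% |
| Beta-binomial on 0–10 | 62% |
| Discrete maximum entropy, 0–10 / 1–10 | 62% / 55% |
| Negative binomial | 64% |
| Gamma, cut at 3 | 54% |
| Scaled beta, cut at 3 | 55% |

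Ordinary shapes give 54–69%. If that share also held before illness, about 31–46% of people, or roughly 35–53 of 115 pairs, would start below the cut and could newly cross it. Mean and SD alone, with no shape assumed, bound the share at or above 3 only between 31% and 90% on a 0–10 scale.

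**Step 3: power if ≥3 status at follow-up is compared within 115 pairs (McNemar).** Let p10 be the proportion of pairs with only the case at ≥3 and p01 the proportion with only the control at ≥3. Put d = p10 − p01 and s = p10 + p01. Then

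power = Φ[(d√n − 1.96√s) / √(s − d²)], and n for 80% = (1.96√s + 0.842√(s − d²))² / d².

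- Normal scores, cut 3: controls 63.1%, cases 74.8%; p10 = 0.251, p01 = 0.134; d = 0.117, s = 0.386. Power = Φ[(1.254 − 1.218)/0.610] = 52%; 220 pairs are needed for 80%.
- Normal scores, cut 2.5: controls 69.1%, cases 79.8%; p10 = 0.225, p01 = 0.119; d = 0.106, s = 0.345. Power = 49%; 238 pairs are needed.
- Simulation with 115 pairs: 53% for normal scores (cut 3) and 61% for beta-binomial scores on 0–10. The paired t test on the same data has 79–80%.

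With no illness effect, both tests reject at about 5%. The problem is lost power, not a false signal.

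**The case against.** The strongest reply is that the cut is attached to the comparison only in one parenthesis of the project summary. The methods, selection and analysis sections (7.5.1, 7.5.2, 7.9) and the sample size section work with the score or its change, and all of these can register a move from 4 to 8. This stands. A reader might infer that the planned endpoint cannot register decline in most matched pairs; the documents do not support that, because only section 3.1.4 points that way. The parenthesis is also ambiguous and could be taken as a change of 3 points or more.

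A reader might also take it as established that most participants already exceed the cut. That does not follow from a mean of 4. It needs an SD and a shape, and it uses the assumed follow-up mean of controls as a stand-in for a pre-illness distribution that the protocol does not report.

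New crossing to ≥3 and ≥3 status at follow-up are different outcomes. The power figures above apply to the second, where people who start at or above 3 still contribute. They should not be read as power for new crossing. Nor does 50–60% power mean that a real effect would mostly go unseen.

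The reply does not remove the inconsistency. Sections 7.5.1 and 7.9 omit the cut but put no other outcome definition in its place. A multinomial model needs categories, and 3 is the only VES-13 boundary that the protocol supplies. An analyst combining 3.1.4 with 7.5.1 could reasonably dichotomise there. This is also not detail left to an analysis plan: the protocol states an outcome rule that disagrees with its own sample-size basis.

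**Conclusion.** The point holds as an inconsistent outcome definition for a secondary objective. Section 3.1.4 names a frailty-status cut, 7.1.5 a paired comparison of the score, 7.5.1 a multinomial model of changes, and 7.9 a comparison of measurements with no cut.

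If 3.1.4 is followed literally as paired ≥3 status, 115 pairs give about 50–60% power rather than 80%, and about 220–240 pairs would be needed under normal scores. This rests on 3 being the per-person SD (the reading that reproduces 115), correlation 0.2, a one-point shift, and normal or beta-binomial scores.

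That a majority would already be at or above 3 is probable under ordinary shapes (54–69%) but is not fixed by the documents. The change should be made, because it corrects a stated rule and brings the outcome into line with the protocol's own sample size.

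**What to change.** Delete the parenthesis giving the VES-13 cut of ≥3 from the comparison sentence in section 3.1.4. Then reconcile 3.1.4, 7.5.1 and 7.9 with 7.1.5 by using one definition throughout: the VES-13 score at the interview three to four weeks after onset, compared within matched pairs and adjusted for each person's most recent prior score. In 7.5.1, replace the multinomial logistic regression with a model for the score that respects the pairing. Report new crossing to ≥3 descriptively only, restricted to people below 3 beforehand.

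The cost is protocol wording. The full score is already collected, and 115 pairs remains the right number on the planning assumptions that reproduce it. The downside is that a mean difference in points is slightly harder to describe than a proportion who are frail.

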## **3.2 Participants**

### **3.2.1 Population participating in the study**

The study will be conducted among males and females aged 65 years and older; this population is recommended for influenza vaccination in Thailand. Data from Thailand and other countries have shown that this age group is at increased risk of severe morbidity and mortality due to influenza-associated ARI.

### **3.2.2 Expected benefit for participants**

There are no expected benefits for participants who enroll in the study.

### **3.2.3 Possible risk if participate in the study**

The risks associated with this study are minimal. There is a very minimal risk of abrasion from improperly taking a nasal swab. Risk will be further minimized by a standardized approach to teaching participants how to safely self-swab. Participants may experience discomfort during collection of nasal and nasopharyngeal swabs, and blood samples, as part of study procedures. Participants may also experience mild redness or soreness at local site of blood draw.

While personally identifiable information will be collected for this study, all data collected will be kept in locked cabinets that only study personnel will have access to. The study team will take all possible steps to minimize risks.

### **3.2.4 Process for obtaining consent**

Written informed consent will be sought from the participants of the community study. Community consent will be sought from all village leaders of the selected sub-district for consent to include their village in the study. Additional consent will be taken in the second year for the immunogenicity sub-study.

### **3.2.5 Participants' protection**

In order to protect the participants, all personally identifiable information obtained from the study will be kept on encrypted and password-protected computers or locked within the study offices in Nakhon Phanom and Nonthaburi and will only be available to staff involved in the study. Personally identifiable information will be stored separately from study information and linked by a unique study identification number. Information that leaves the study offices in Nakhon Phanom will have no personal identifying information linking the participants to either the study or their responses.

## **4. Introduction and background**

### **4.1 Importance and reasons for conducting study in human subjects**

Influenza vaccination is recommended for all persons  $\geq 65$  years. Ongoing monitoring and evaluation of this program is important in order to document the effects of the vaccine and justify the continuation of the program. Critical outcomes to monitor include vaccine uptake, cost and efficacy. Because vaccine is recommended, it is not ethical to do a randomized controlled trial. Using an observational cohort study, we will be able to generate high quality data on VE in this age group, improving on previous studies by using a population-based cohort and confirming influenza infection through use of molecular diagnostics. Information from a concurrent study of predictors of vaccine coverage will provide information on potential confounders of the association between vaccination and disease reduction, improving the validity of VE results. Additionally, data on cost will be collected to determine value for money of the vaccination campaign in preventing cases and additional health care costs.

### **4.2 Literature review**

Elderly patients are at increased risk for severe complications and mortality due to influenza infection. The elderly, defined as adults  $\geq 65$  years, are at an increased risk for influenza-associated hospitalizations and death compared to adults  $<65$  years of age(12) . The elderly are more susceptible to experiencing complications of influenza-pneumonia which include the exacerbation of underlying medical conditions such as cardiac health and lung

disease (13). Between 2005 and 2008, influenza-pneumonia was responsible for approximately 36,413 annual hospital admissions and 322 in-hospital deaths in Thailand (13). During this same time, the annual incidence of influenza pneumonia in Thailand was highest in patients 75 years of age or older (13). Complications due to influenza also have the potential to decrease functional status and quality of life in the elderly (14). In order to prevent influenza morbidity and mortality, Thailand's Ministry of Public Health (MOPH) began a vaccine campaign in 2009 to vaccinate high-risk influenza groups including adults  $\geq 65$  years of age with IIV3.

Studies among adults  $< 65$  years of age and children have shown vaccine efficacy and effectiveness in preventing influenza. A 2012 meta-analysis found a vaccine efficacy ranging from 51% to 67% among adults  $< 65$  years for laboratory-confirmed influenza, and a large multi-site observational study found VE for laboratory confirmed influenza ranging between 54% and 66% among children 6 months to 8 years in 2010-2011 (15). Elderly persons are known to mount a less robust immune response to vaccines in general, and lab-confirmed influenza VE among the elderly is generally lower than that seen for adults and children. A large randomized efficacy study reporting vaccine efficacy against lab confirmed influenza for adults  $\geq 60$  found a range between 26% and 77% in a season when circulating influenza strains were well-matched to the vaccine(15). Data on the effectiveness of the seasonal, trivalent IIV in Thailand are scarce. Among the elderly, only three studies have been conducted in Thailand: one found that IIV reduced hospitalizations among adults  $\geq 50$  years due to laboratory-confirmed influenza-associated ARI by 47% using a test-negative case control approach that included only hospitalized patients (12); in the second, a randomized, controlled trial, IIV prevented 56% of influenza-like illnesses among adults  $\geq 60$  years, although these were not laboratory-confirmed influenza cases (16). The third study, a nonrandomized, controlled, prospective cohort study conducted in Bangkok found a 47.6% vaccine effectiveness rate and about half reduction in incidence of influenza like illness (ILI) in adults  $\geq 60$  years that were vaccinated compared to elderly that were not vaccinated, but major limitations to this study and its results include non-randomization as well as non-laboratory confirmed influenza(17). The studies that show hospital and mortality reduction among the elderly who were vaccinated are mostly retrospective and do not have laboratory confirmed influenza data (15).

Immunogenicity studies have been used to test the antibody response of influenza vaccines by quantifying the amount of antibody seroconversion and duration of humoral immune

response post influenza vaccination, and results have been inconsistent among elderly (15). A literature review of 31 studies between 1986 and 2002 comparing influenza antibody response between adults >58 years of age and adults between the ages of 17 and 59 found that the elderly had overall 2 to 4 times lower rates of seroconversion compared to younger adults(18). Another literature review published in 2008 showed that rapid decline of antibody response among elderly within months of receiving the influenza vaccine was not correlated with age(19). Some studies conducted among children and adults suggest that prior influenza vaccinations and higher levels of preexisting serum HAI antibodies may decrease immunologic response to subsequent vaccination (20-22). Confounding between age and number of prior vaccinations could explain a lower serologic response to vaccination in older adults. A longitudinal cohort study measuring trivalent vaccine effectiveness using laboratory confirmed influenza and measuring humoral immune response among the elderly will lead to more definitive answers.

Elderly with certain underlying medical conditions, such as chronic obstructive pulmonary disease (COPD), are especially at high risk from influenza. COPD is a respiratory illness characterized by irreversible airflow obstruction. In 2010, COPD was the sixth leading cause of death in Thailand (23), and in 2002, the prevalence of COPD among the elderly around Bangkok was 7.11 percent(24). Influenza exacerbates COPD symptoms, and vaccinating individuals with COPD can reduce the risk of hospitalizations, morbidity and mortality (25). One study from the United Kingdom showed that influenza vaccination reduced the risk of all-cause mortality in COPD patients by 41% between December and March(26). Another study conducted in the United states among elderly persons with COPD found that the risk of hospitalization due to pneumonia or influenza was reduced by 48% from influenza vaccination (27). A study conducted in the United States among elderly persons during the influenza season found hospitalization costs due to acute and chronic respiratory conditions to be 42% lower in those that were vaccinated (28). A cost effectiveness analysis in Thailand found that depending on the severity of COPD, for every 100 persons with COPD that receive the influenza vaccine, roughly 125,629 to 680,647 Thai Baht was saved (29, 30). To date, there is only one study that examined vaccine efficacy among persons with COPD who were mostly elderly in Thailand. This randomized controlled trial of the efficacy of IIV3 among persons with COPD in Bangkok, Thailand, to prevent influenza-associated ARI found a vaccine effectiveness (VE) of 76% (30). Because the Thailand MOPH is prioritizing adults with COPD to be vaccinated with influenza, and the

elderly with COPD are at heightened risk, more research is needed to confirm the vaccine effectiveness of trivalent IIV3 influenza vaccine among the elderly with COPD in Thailand to support future protocols.

Data on the cost-effectiveness of vaccinating the elderly is also scarce and still needs to be established in Thailand. Because the elderly are at highest risk for costly hospitalizations due to influenza, vaccinating the elderly has shown to be cost-effective across many Western parts of the world (31). Establishing the cost effectiveness of vaccinating elderly in the subtropics has been more difficult, possibly due to the variable seasonality of influenza in the area (31). Despite evidence that influenza costs Thailand between 23.4 and 62.9 million US dollars annually in economic losses (32), and data showing that IIV3 is cost effective for COPD patients, at least one study has suggested that vaccination in the elderly may not provide sufficient value for money (16). This study found that vaccination significantly reduced the incidence of influenza by about half, but did not reduce the incidence of influenza like illness (ILI) nor the cost associated with treatment of ILI (16). In this study, though, none of the participants acquired pneumonia or needed hospitalization during the study period (16). Further data on the cost-effectiveness of IIV3 for persons aged 65 years or older in Thailand are needed to support increases in coverage.

Functional status encompasses the ability to execute self-care, self-maintenance and perform physical activities. Having ARIs or SARIs may impact the short-term and long-term functional status of the elderly, and vaccinating elderly with influenza to reduce the number of ARIs and SARIs they experience could positively impact their functional status (14). On the other hand, studies have shown that functional status of elderly can impact efficacy of influenza vaccination (33, 34). Lower levels of functional status may be associated with a higher risk of death and a lower probability of influenza vaccination, thus, functional status may confound the association of influenza vaccination and risk of all-cause mortality in the elderly (35). Functional status is being recognized as a potential confounding factor in many influenza vaccine effectiveness studies (35-40). By recording functional status, it can be adjusted for as a confounder when calculating vaccine effectiveness, and it can be used to determine if there is an association between experiencing ARIs and SARIs and having a change in functional status among the elderly.

While influenza A is the main cause of respiratory infections in older adults, other viruses present similarly and also contribute to burden (41). Respiratory syncytial virus (RSV) causes lower respiratory lung infections including pneumonia, most commonly in young children (42). There is little information available on the incidence of RSV among older adults and the elderly, and even less on the elderly in Thailand. In the United States, an estimated 9,812 deaths occur annually due to RSV among the elderly and over 78% of RSV-associated underlying respiratory and circulatory deaths occurred in adults 65 years of age or older(43). A prospective cohort study following high risk adults and elderly patients from Rochester, New York, found that RSV resulted in 10.6 percent of the hospitalizations for pneumonia and 11.4 percent for COPD (44). This study also found that patients who were hospitalized for RSV had similar lengths of stay, use of intensive care unit, and mortality to those hospitalized due to influenza A (44). In a study in Thailand between 2008 and 2011, 3.8% of hospitalized adults  $\geq 65$  years with acute lower respiratory infection (ALRI) tested positive for RSV (42). The same study found that RSV results in about 130 ALRI hospitalizations for every 100,000 elderly adults infected (42). According to another study in Thailand, 2.9% of adults  $\geq 50$  years who were hospitalized for pneumonia tested positive for RSV (41). While these studies examine the incidence of RSV-associated hospitalizations, they do not account for the burden of RSV-associated ARI in the community in Thailand, for which no data are currently available. Symptoms of RSV are similar to influenza and include fever, runny nose, cough and decreased appetite (45). RSV, like influenza, can be identified using rRT-PCR. Because participants in the study will already have respiratory swabs taken when experiencing ARI or SARI (symptoms related to both influenza and RSV), we will test for both viruses to add on to our current knowledge of RSV incidence among the elderly and determine the burden of RSV in both the community and hospital settings.

